#### Ethical principles

The participation in the study is voluntary. Participants are informed that they can cancel their participation at any time without disclosing reasons for their cancellation and without negative consequences for their future care. Participants will sign an informed consent.

#### Vote of the ethics committee

The design and conduct of the study was approved by the Medical Ethics Committee of the VU University Medical Center, Amsterdam.

## Discussion

This study protocol is presented here to offer researchers the opportunity to consider the methodological quality of this study with a critical view. Therapists can benefit by considering the information regarding the practical applications of the proposed protocol on chronically depressed patients in secondary care.

The number of studies examining the effects of psychotherapy on chronically depressed patients is very small, while chronic depression affects a large group of patients in secondary care and this subgroup is notable for poorer subjective well being and impaired social and occupational functioning compared to non-chronically depressed patients [10]. Research into the effectiveness of CBASP can make an important contribution to the improvement of care for chronically depressed patients. According to the results of Keller et al. (2000), 73% of these patients can be effectively treated if CBASP is combined with antidepressant medication. CBASP can also be an alternative for patients who are not motivated for or refractory to pharmacological treatment. Furthermore, CBASP could also be effective as a maintenance treatment [13-17].

### Strengths and limitations

Many methodological requirements for a high quality trial are met. Allocation is concealed through randomization by an external researcher. Recruitment of the patients will be done after the standard intake procedure at each site. As this study takes place within the mood disorder departments of three organizations for mental health care in the Netherlands the results can, to a large extent, be generalized to the population of chronically depressed patients seen in secondary care in the Netherlands.

A limitation of the present study is that the assessments will be performed by research nursing staff who cannot be kept blind to the treatment condition of the included patients, as is always the case in trials studying the effects of psychotherapy. Nor are the patients blind to treatment condition. In this study, however, the main outcome measures are self-report questionnaires, which means that they will not be influenced by the research nursing staff.

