#### Assessments

Data are collected at five points in time: at baseline (T0), after 8 weeks of treatment (T1), after 16 weeks of treatment (T2), after 32 weeks of treatment (T3), and at the endpoint, after 52 weeks of treatment (T4). The Quick Inventory of Depressive Symptomatology self-report [23] will be assessed monthly. Table 1 summarizes the measures that are used at each point. The assessments will be performed by an experienced research nursing staff. At baseline and endpoint there will be a face-to-face interview besides the written questionnaires; the three assessments in between consist of written questionnaires only. The research nursing staff from the three participating organizations will participate in a two-day training course to make sure the measures are conducted the same way at the different locations.

**Table 1 T1:** Summary of measures

**Measure**	**Baseline**	**8 week follow-up**	**16 week follow-up**	**32 week follow-up**	**52 week follow-up**

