**Questionnaires for economic evaluation:**					
Registration of usage medication	x				x
TIC-P measures illness and work	x				x
Perceived need for care	x				x
TIC-P work + health care utalization self report			x	x	

**Questionnaires filled in by therapists:**	**Baseline**	**8 week follow-up**	**16 week follow-up**	**32 week follow-up**	**52 week follow-up**

Clinical Global Impression-Improvement (CGI)		x	x	x	x
Working alliance questionnaire, therapist version		x	x	x	

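### The article treats unblinded assessors as unavoidable in psychotherapy trials, so the week-52 M.I.N.I. plus diagnosis is left to nurses who know the arm

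*Protocol article*

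**What the plan says.** Strengths and limitations (Discussion) names as a limitation that assessments are made by "research nursing staff who cannot be kept blind to the treatment condition of the included patients, as is always the case" in psychotherapy trials. It adds: "Nor are the patients blind to treatment condition". It then offers a mitigation: "the main outcome measures are self-report questionnaires, which means that they will not be influenced by the research nursing staff".

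The Assessments section states: "The assessments will be performed by an experienced research nursing staff". On the mode of contact it says: "At baseline and endpoint there will be a face-to-face interview besides the written questionnaires". Weeks 8, 16 and 32 use written forms alone. On preparation it says: "The research nursing staff from the three participating organizations will participate in a two-day training course", so that the measures are taken alike at all locations.

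Table 1 lists the M.I.N.I. plus in its interview block, at baseline and week 52. The section on secondary measures of outcome and predictors of response also places it at the start and end of the study. The IDS is in the self-report block, and the CGI is among the forms filled in by therapists.

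**The concern.** The limitation is worded as though it came with every psychotherapy trial. If that were so, nothing could be done beyond disclosing it. But it joins two different things. Those who receive or deliver a psychotherapy necessarily know what it is. Someone who only conducts an interview a year later need not know.

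What is at stake is the week-52 diagnosis. The M.I.N.I. plus is structured, which limits the interviewer's discretion but does not remove it. Whether a symptom counts as present is still partly a judgement, and a rater who knows the arm may lean one way on borderline answers. A between-arm difference in diagnosis at one year would then mix any treatment effect with rater expectation, and the data would not allow the two to be separated.

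**Working it through.** The point challenges no figure in the article, so no arithmetic applies. The check sets the statements side by side.

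1. **Who makes the week-52 diagnosis?** Assessments gives the assessments to research nursing staff and includes an interview at week 52. Table 1 puts the M.I.N.I. plus in that interview. Read together, the nurses make the diagnosis.

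2. **Do they know the arm?** Strengths and limitations says they cannot be kept blind. No independent or blinded rater is described for any outcome.

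3. **Is baseline affected?** No. Under Randomization, allocation follows completion of the baseline interview. Only the week-52 diagnosis is exposed.

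4. **Does the self-report argument cover it?** No. That argument concerns questionnaires that patients fill in. The M.I.N.I. plus is an interview recorded by the nurse.

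5. **Is blinding the interviewer ruled out by the design?** Nothing in the article rules it out. Three organisations take part (Recruitment/Settings and locations). Their nurses share one training course meant to make the measures uniform, so a nurse from one organisation should be able to interview a patient of another. Allocation is already handled by an external researcher (Randomization), so the allocation need not pass through the interviewer.

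6. **What could reveal the arm at that visit?** Table 1 also schedules medication registration, the TIC-P and perceived need for care at week 52. The Economic evaluation section says patients fill out the TIC-P and the need-for-care form, but Table 1 calls only the week-16 and week-32 TIC-P self-report. If the interviewer handles these items before recording the diagnosis, the answers could disclose the treatment.

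7. **Is the primary IDS affected by the nurses?** Not at weeks 8, 16 and 32 on the article's account, since those are written forms only. Week 52 is the only IDS time point after allocation that is paired with an interview. The article does not say whether the form is completed before or after that interview, or in whose presence. Influence is possible there but not shown. The assurance "which means that they will not be influenced by the research nursing staff" is therefore firmer than the described procedure supports.

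**The case against.** The strongest reply is that the article has already disclosed the weakness. It lists unblinded assessors as a limitation, admits that patients are unblinded, and bases its main outcome on self-report. The sample size rests on response, which is defined on the IDS, and the Analysis section estimates the treatment effect on the IDS. Neither uses the M.I.N.I. plus. All of this stands, and it keeps the point modest. It does not make the word always correct, and it does not protect the diagnosis.

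A reader might infer more than the document supports:

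- **That the article declares self-report safe from bias.** It claims only freedom from influence by the nurses.
- **That the week-52 IDS is contaminated by the interviewer.** Order and setting are not stated, and a condensed article may leave them to the full protocol. Nor would a blinded nurse remove the main weakness of the IDS, which is that the patient who rates it knows the treatment.
- **That the CGI fails for the same reason.** It is unblinded because therapists complete it, and blinding the nurses would change nothing. The article states no between-arm CGI test. Usual care may include recognised psychotherapies, so control patients may also have a psychotherapist as rater.
- **That the trial relies on the M.I.N.I. plus or CGI to corroborate the IDS.** The article gives them no such role.
- **That a number can be put on the bias.** Any misrating rate would be invented. Setting a shift in diagnosis against the planned 25% gain in response would compare two different outcomes.

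A practical objection also stands in part. An unaware interviewer may learn the arm from the patient or from the care-use items, so the visit has to be split or ordered with care.

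**Conclusion.** The point holds in a limited form. The article is wrong that assessors in psychotherapy trials can never be blind. As a result, one secondary measure at one time point, the week-52 M.I.N.I. plus, is rated by staff who know the arm when this could be avoided. The likely direction of bias depends on the raters' expectations, and its size cannot be derived from the document.

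The conclusion assumes that the nurses conduct the week-52 interview, as Assessments and Table 1 together indicate, and that the diagnosis leaves some room for judgement. A blinded interviewer would remove only the rater's share of the bias, because the patient answering still knows the treatment. The primary IDS comparison and the sample size are not called into question. This is a cheap improvement of modest weight.

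**What to change.** 1. Have the week-52 M.I.N.I. plus done, in person or by telephone, by an already trained research nurse of another participating organisation who is not told the allocation. Ask the patient not to mention treatment, and have the nurse record a guess of the arm.
2. Collect the medication, care-use and need-for-care items separately, or after the diagnosis has been recorded.
3. If step 1 is not adopted, report the M.I.N.I. plus as an unblinded rating.
4. Have the week-52 IDS completed before the interview.
5. Reword Strengths and limitations to say that therapists and patients cannot be blinded, and that self-report reduces assessor influence but leaves the expectation bias of unblinded patients.
6. Label the CGI as therapist-rated and unblinded.

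Step 1 costs scheduling and, for interviews in person, travel between sites in Amsterdam and The Hague. Step 2 may mean splitting the visit. The rest is ordering and wording. No new staff are needed, and neither sample size nor treatment changes.

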### Timeframe of the study

In October 2006 a pilot study, supervised by [name], has started to enable the therapists to gain experience with this innovative intervention. In May 2007 the randomized treatment study has been started up. Month 1–12: Screening and inclusion of chronically depressed patients at the three locations. Start of the data collection for the treatment study. Supervision of the treatments. Start of data entry and purging of databases. Month 13–24: Completion of data collection. Completion of purging and analysis of the data. Publication on these short-term findings.

Month 24–36: Completion of data collection of the follow-up. Publication on the effectiveness of CBASP and the follow-up effects. Dissemination of the results (e.g. presentation of study results at national and international conferences). Working on the implementation of CBASP in the Netherlands.

### Description of risks

There are no specific risks related to this study.
